### Study groups

#### Group 1: photobiomodulation therapy

The participants in this group will be submitted to laser therapy five times a week, during the RT. The PBMT protocol will begin in the first RT session, be conducted before each RT session and continue until the end of the treatment. Since the RT sessions will be scheduled in a specific hour, it will be possible to control participant appointments. If severe OM develops at the end of the RT, the patient will receive additional sessions.

The Twin Flex Evolution Laser (MMOptics, São Paulo, Brazil) will be used at a wavelength of 660 nm (red laser), 25 mW of power, in continuous mode, with punctual and perpendicular application in contact with the mucosa. The transferred energy will be 6.2 J/cm^2^ for 10 s on a spot area of 0.04 cm^2^, and thus energy of approximately 0.25 J will be deposited at each point. Before each session, the tip of the laser will be disinfected with a solution of 70% alcohol and wrapped in a plastic film. The laser beam will not be irradiated in a malignant lesion smaller than 1 cm if observed, or near a surgical site.

Specific anatomical regions be considered for the PBMT: right and left buccal mucosa (10 points on each side), upper and lower labial mucosa (four points on each lip), hard palate (three points), lateral surface of the tongue (10 points on each side), soft palate (three points), dorsal tongue (three points), floor of the mouth (two points) and labial commissure (one point on each side). This protocol is based on a previous study by Oton-Leite et al. [30].

The participants will also be submitted to a dental care protocol that consists of elimination of the infection focus, a fluoride rinse, a chlorhexidine 0.12% rinse three times a day diluted in water in a 1:1 proportion, recommendation to drink at least 1.5 L of water per day and the maintenance of good oral hygiene. If the presence of OM is observed, an oral ointment with hydrocortisone 5 mg, neomycin 5 mg, troxerutin 20 mg, ascorbic acid 0.5 mg and benzocaine 2 mg will be prescribed (Gingilone; Farmasa, São Paulo, Brazil).

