## Background

The association of chemotherapy (CT) and radiotherapy (RT) is the most frequent treatment approach for head and neck cancer (HNC) in cases of locally advanced disease [1]. Oral mucositis (OM) is the main side effect of RT and chemoradiation therapy (CRT) for HNC, its severity dependent on the number of RT sessions [2–6]. OM is an inflammatory reaction that can affect the entire oral cavity and gastrointestinal tract [7–10]. Intense pain, the need for nutritional supplementation, a higher number of clinical appointments and treatment interruption are common events associated with severe OM. These side effects may influence the survival rate and increase the costs of the HNC treatment [3, 5, 11–14].

CT and RT increase the levels of reactive oxygen species that may cause upregulation of transcription factors, such as NF-κB and STAT3 [4]. This increased level of transcription factors activates the production of inflammatory cytokines, such as matrix metalloproteinase, leading to tissue damage [4, 5, 15]. The use of photobiomodulation therapy (PBMT) has been encouraged and is described as effective therapy for OM treatment [16, 17]. Recent data showed that PBMT improves quality of life (QoL) and is effective in the control of OM, reducing the morbidity and costs associated with OM [16–24]. Oberoi et al. [18] concluded that PBMT reduced the number of severe OM episodes and pain associated with it. However, several protocols for PBMT have been described with differences in the laser wavelength, time of irradiation, frequency and energy used. They suggested that research should be conducted investigating the ideal parameters and clinical viability.

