### Participants

The participants will be HNC patients of the Brazilian public health system—Brazilian Unified Health System (Sistema Único de Saúde (SUS))—who will be treated with RT, with or without CT, in Araujo Jorge Hospital, Goiânia, Goiás, Brazil. To estimate the study sample size, we used the OpenEpi online calculator (http://www.openepi.com). The 95% significance level (1 – α error type I), a study power of 80% (1 – β error type II) and a 1.0 ratio of unexposed/exposed were set as estimator parameters. Finally, we considered a prevalence of severe OM of 60% for the control group and 21% for the PBMT group (OR = 0.18) [18]. The calculated minimum sample size was 50 participants (25 per group) and an additional 10% was considered to compensate for possible loss to follow-up.

Individuals older than 18 years of age of both sexes will be included in the study, edentulous or not, with neoplastic lesions in the head and neck site (oral cavity, oropharynx, nasopharynx and advanced stage laryngeal tumors; T3 N1 or T3 N2 and T4 with any N status). All participants will be subjected to RT (with or without CT), with a minimum dose of 50 Gy, 2 Gy/day and five times per week, in the conventional scheme of RT. All patients will be treated with the Elekta Compact (Elekta AB, Stockholm, Sweden), a linear accelerator that generates photon radiation with fixed energy of 6 MV. Participants will be excluded if they present with an infection or salivary gland tumors, Sjögren’s syndrome, are submitted to palliative treatment or were previously treated with RT and/or CT in the head and neck area. Individuals diagnosed with lymphoma, melanoma or skin cancer will also be excluded.

In this hospital setting, every HNC patient who will be submitted to RT must be evaluated by the Dental Care Service to obtain authorization before starting the HNC treatment. On this occasion, the individuals will be invited to participate in the study. After acceptance, the principle researcher will obtain a signed written informed consent form from the participants. Participants will be excluded from the trial in cases of death, withdrawal or absence from five or more laser therapy sessions.

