#### Oral mucositis evaluation

An assessor who is blinded to the treatment will conduct the OM evaluation. The researcher responsible for the PBMT will take intraoral pictures and save them on a hard disk for later evaluation. The evaluation will be in the first appointment and after the 7th, 14th, 21st and 30th RT sessions. The photographs will be taken using a T3i camera, with a circular flash (MR-14EX II) and a lens of Ef-s 18–55 mm F/3.5–5.6 (Canon, Tokyo, Japan). Pictures of the upper and lower labial mucosa, buccal mucosa, hard and soft palate, lateral surface of the tongue and floor of mouth will be acquired.

For the OM classification, the World Health Organization (WHO) [31] and the National Cancer Institute (NCI) [32] classifications will be used.

According to the WHO scale, the OM is classified as: 0, no signs or symptoms; 1, oral soreness and erythema; 2, erythema, ulcer, both solid and liquid diets tolerated; 3, ulcers and liquid diet only; 4, oral alimentation is impossible. The NCI scale is a graduated scale as follows: 0, no visible alterations; 1, presence of erythema; 2, noncontiguous ulcers up to 1.5 cm in diameter; 3, contiguous ulcers larger than 1.5 cm in diameter; 4, ulcers showing necrosis and bleeding. In this study, OM will be considered severe when classified with grades 3 or 4 according to the NCI and/or WHO scales.

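### The only tumour-sparing sentence protects malignant lesions under 1 cm and gives no instruction for visible unresected lesions of 1 cm or more

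*Protocol article*

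**What the plan says.** The Group 1 section of the Protocol article describes "punctual and perpendicular application in contact with the mucosa" at a fixed list of intra-oral regions. The list includes the buccal and labial mucosa, the lateral tongue, the hard palate and "soft palate (three points), dorsal tongue (three points), floor of the mouth (two points" each counted separately). Sessions run five times a week throughout radiotherapy (RT).

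The same section has one sentence on sparing tumour: "The laser beam will not be irradiated in a malignant lesion smaller than" 1 cm "if observed, or near a surgical site".

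The Participants section makes these sites eligible: "oral cavity, oropharynx, nasopharynx and advanced stage laryngeal tumors". It names T3 and T4 stages, though the punctuation leaves open whether the stage limit covers every site or only the larynx. Treatment is described as "All participants will be subjected to RT (with or without CT"). Prior resection is not required, and a visible intra-oral lesion is not among the exclusions.

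The Group 2 section gives real PBMT to controls when RT is suspended for severe oral mucositis, and at the end of RT if needed. It adds no sparing rule of its own.

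**The concern.** A rule that keeps the beam off small tumours should also keep it off larger ones. The printed sentence covers only the small ones. For a larger lesion that is still in place, the operator has a point map that includes the site and no stated exception.

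What is at stake is a participant-safety instruction and the reproducibility of the intervention. The article's Discussion reports a cited paper that raised possible effects of PBMT on tumour growth and discouraged its use. It also reports guideline support and favourable survival data. The authors therefore treat tumour exposure as a live question, and the one operative sentence on it should be clear.

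**Working it through.** No figure in the article depends on this sentence, so the check is a reading of the relevant sections side by side.

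**1. Which lesions does the rule cover?** There are two triggers: a malignant lesion under 1 cm, if seen, and proximity to a surgical site. The second deals with tumours already resected. What remains uncovered is a visible lesion of 1 cm or more that is still in place.

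**2. Does another section cover it?** The Group 1 and Group 2 sections, the eligibility criteria and the Discussion were read for a further rule. None sets one. The Discussion's paragraph on tumour effects is background and gives no instruction on application.

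**3. Does the point map reach such lesions?** The mapped points are:

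- buccal mucosa 2 × 10 = 20
- labial mucosa 2 × 4 = 8
- hard palate 3
- lateral tongue 2 × 10 = 20
- soft palate 3
- dorsal tongue 3
- floor of mouth 2
- commissures 2 × 1 = 2

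The total is 20 + 8 + 3 + 20 + 3 + 3 + 2 + 2 = 61. All are intra-oral or at the lips. Nasopharynx and larynx are not mapped, so tumours at those sites are outside the gap. It concerns oral-cavity tumours, and oropharynx tumours only where they extend to a mapped point such as the soft palate.

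**4. Can such participants be enrolled?** Yes. Both sites are eligible, no upper size limit is set, resection is not required, and none of the listed exclusions removes a visible lesion. The Background says that combined chemotherapy and RT "is the most frequent treatment approach for head and neck cancer (HNC) in cases of locally advanced disease". That is consistent with enrolling unresected tumours but does not prove it, because it does not say surgery is omitted.

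**5. Do the two plausible readings differ in practice?** Take a visible unresected 2 cm lesion on the lateral tongue.

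| Reading | Guidance at that lesion |
|---|---|
| As printed (size under 1 cm) | No instruction to withhold; the map lists the region |
| As a distance (within 1 cm of a lesion) | Withhold |

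The readings part exactly where a sparing rule is needed.

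**The case against.** The strongest reply is that this is a condensed article. Operator instructions may sit in the full protocol or in the earlier study on which the laser protocol is based, and neither is shown. The treatment is given by a dentist licensed in PBMT, who may well avoid tumour whatever this sentence says. This stands as a limit: nothing can be concluded about what operators were told or did. It does not remove the point, because the article states a rule and states it badly, which is different from leaving a detail out.

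A reader might infer that the protocol orders irradiation of large tumours. It does not. The text is silent on them, and a list of regions to be treated in contact with mucosa is not an order to treat tumour. The narrower statement holds: the map is the default, and the printed exception does not extend to larger lesions.

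It is also fair to say that exposure is inferred. The surgical-site clause shows that operated patients are expected, and the article does not say how many participants would have an unresected lesion at a mapped point.

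Finally, the Discussion's aim of a safety evidence-based protocol describes what the investigators hope to produce. It does not set a standard for this sentence, and the point does not need it.

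**Conclusion.** The concern holds as a defect in one stated safety rule. The size condition makes no sense as written and leaves visible unresected malignant lesions of 1 cm or more at mapped contact points without an instruction. A slip for a 1 cm distance is the likely explanation, but that is an inference.

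The size of the problem cannot be given, because the number of participants with such a lesion is neither stated nor derivable. The conclusion rests on the eligibility text permitting these participants, not on evidence that any were enrolled.

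A reader might go further and infer that PBMT harms tumours, or that the trial's results are compromised. The article supports neither: it reports views on both sides of the tumour question, and no outcome, sample-size or cost-effectiveness figure depends on this sentence. The correction should be made because it is cheap and concerns participant safety.

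**What to change.** Replace the sentence in the Group 1 section with:

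> *The laser will not be applied on any visible malignant lesion, whatever its size, or near a surgical site.*

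Ask the sponsor whether 1 cm was meant as a size or a margin. If a margin, add *or within 1 cm of it* after *whatever its size*. State in the Group 2 section that the same rule applies to rescue PBMT in controls.

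The downside is that some mapped points are omitted in participants with visible intra-oral tumour, so they receive a lower total dose.

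The cost is one sentence, one cross-reference and one sponsor confirmation, with no change to sample size, visits or analysis. Recruitment and treatment began in August 2017 under two ethics approvals. If operators already spare all visible tumour, this is only a correction of the text. If they do not, it changes the intervention during the trial and should be handled as such with both committees.

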#### Group 2: control group

The participants in the control group will have laser therapy appointments; however, they will not be irradiated. A simulation of the irradiation will be conducted by turning on the equipment, which produces the characteristic sound of the laser device, but the laser will not be irradiated. As mentioned for the PBMT group, if participants present with severe OM at the end of treatment, they will be submitted to PBMT. The participants will also be submitted to laser therapy in cases of RT suspension due to severe OM, during the suspension interval, to speed up the healing process.

The participants in the control group will be submitted to the dental care protocol. This protocol consists of elimination of the infection focus, a fluoride rinse, a chlorhexidine 0.12% rinse three times a day diluted in water in a 1:1 proportion, a recommendation to drink at least 1.5 L of water and the maintenance of good oral hygiene. In the presence of OM, Gingilone (Farmasa), an oral ointment with hydrocortisone 5 mg, neomycin 5 mg, troxerutin 20 mg, ascorbic acid 0.5 mg and benzocaine 2 mg, will be used. At the end of the RT treatment, the participants in this group will also receive PBMT if needed.

### Outcomes

The effectiveness of the treatment will be measured based on severe OM being prevented and by the impact on the QoL of the participants. The levels of inflammatory cytokines in saliva will also be investigated.

#### Oral mucositis evaluation

An assessor who is blinded to the treatment will conduct the OM evaluation. The researcher responsible for the PBMT will take intraoral pictures and save them on a hard disk for later evaluation. The evaluation will be in the first appointment and after the 7th, 14th, 21st and 30th RT sessions. The photographs will be taken using a T3i camera, with a circular flash (MR-14EX II) and a lens of Ef-s 18–55 mm F/3.5–5.6 (Canon, Tokyo, Japan). Pictures of the upper and lower labial mucosa, buccal mucosa, hard and soft palate, lateral surface of the tongue and floor of mouth will be acquired.

For the OM classification, the World Health Organization (WHO) [31] and the National Cancer Institute (NCI) [32] classifications will be used.

According to the WHO scale, the OM is classified as: 0, no signs or symptoms; 1, oral soreness and erythema; 2, erythema, ulcer, both solid and liquid diets tolerated; 3, ulcers and liquid diet only; 4, oral alimentation is impossible. The NCI scale is a graduated scale as follows: 0, no visible alterations; 1, presence of erythema; 2, noncontiguous ulcers up to 1.5 cm in diameter; 3, contiguous ulcers larger than 1.5 cm in diameter; 4, ulcers showing necrosis and bleeding. In this study, OM will be considered severe when classified with grades 3 or 4 according to the NCI and/or WHO scales.

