#### Quality of life

The translated, adapted and validated Brazilian version [33] of the Oral Health Impact Profile, in its simplified form (OHIP-14) [34], will be used to assess the oral health-related quality of the participants. This questionnaire contains 14 questions, divided into seven subscales: functional limitation, physical pain, physiological discomfort, physical disability, physiological disability, social disability and handicap. The questions will be answered on a 5-point Likert scale, the responses will be summarized and the final score will be calculated.

The translated version of the Patient-Reported Oral Mucositis Symptoms (PROMS) scale will also be used to assess the OM effects reported by the patient [35]. This scale was originally used to assess OM due to CT; however, its use in patients undergoing RT is also feasible [36, 37]. The scale contains 10 questions, which are answered on a 10-cm uninterrupted visual analog scale. The participant will be asked to indicate the score for each item. The sum of the 10 items will be used as the PROMS score.

These instruments will be applied during the first appointment and after the 7th, 14th, 21st and 30th RT sessions based on previous studies [23, 38] that also evaluated the QoL weekly. As reported earlier, the OM evaluation will occur at the same time points. The questionnaires will be applied before the PBMT session and if the participant is not able to answer, a calibrated healthcare professional will provide help.

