##### Costs due to severe OM

The costs related to OM will include episodes of severe OM (WHO degrees III and IV), hospitalizations, use of opioid analgesics and parenteral nutrition. These data will be retrieved from the hospital records and cost estimation will be based on the governmental database for the public health system.

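### Oral mucositis is graded at 8- to 13-day gaps on a session clock that stops when radiotherapy is suspended, so a severe episode that halts treatment can go unrecorded

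*Protocol article*

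**What the plan says.** - **Grading schedule** (Oral mucositis evaluation): "The evaluation will be in the first appointment and after the 7th, 14th, 21st and 30th RT sessions". A blinded assessor grades photographs. Severe means grade 3 or 4 on the NCI and/or WHO scale.
- **Fractionation** (Participants): RT is given "with a minimum dose of 50 Gy, 2 Gy/day and five times per week".
- **Basis for the time points** (Quality of life): the questionnaire schedule is "based on previous studies [23, 38] that also evaluated the QoL weekly", and "the OM evaluation will occur at the same time points".
- **Suspension** (Group 2: control group): controls also receive active laser "in cases of RT suspension due to severe OM, during the suspension interval, to speed up the healing process". The section on Group 1 ties laser to RT sessions and has no matching provision. Neither section states an OM grading at or during suspension.
- **Use of the outcome**: severe OM sized the trial (Participants, 60% versus 21%) and is the denominator of one incremental cost-effectiveness ratio (ICER) (Cost-effectiveness analysis).
- **Costs** (Costs due to severe OM): severe episodes of WHO degree III and IV, hospitalizations, opioids and parenteral nutrition are costed. "These data will be retrieved from the hospital records".

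**The concern.** The numbers 7, 14 and 21 would be weekly as calendar days, but they count sessions given five per week. The real gaps are longer, and the last one is the widest or joint widest, although the Background says severity depends on the number of sessions.

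The sharper problem is suspension. Take a participant who is not severe at session 21, is suspended for severe OM a few sessions later, heals during the break, and is still below grade 3 at session 30. Followed as written, the schedule holds no severe grade for a participant whose severe OM stopped RT. The article itself anticipates this event in controls and describes healing-directed treatment during the break.

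Two quantities are at stake: the frequency of severe OM in each arm, and the consistency of the ICER. Costs come from hospital records, which do not follow the session clock. An episode can then enter the numerator while its event is absent from the denominator.

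**Working it through.** **1. The plan's own sample size.** Inputs (Participants): 60% and 21%, 80% power, 5% significance (two-sided assumed), 1:1. The Kelsey formula gives 24.87, so 25 per group, which matches the stated 50. The odds ratio is (0.21/0.79)/(0.60/0.40) = 0.177, matching 0.18. Approximate power at 25 per group is 82%.

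**2. Sessions to calendar days** (five per week, weekends off, no suspension).

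| First session | Days elapsed at sessions 1, 7, 14, 21, 30 | Gaps (days) |
|---|---|---|
| Monday | 0, 8, 17, 28, 39 | 8, 9, 11, 11 |
| Tuesday | 0, 8, 17, 28, 41 | 8, 9, 11, 13 |
| Wednesday or Thursday | 0, 8, 19, 28, 41 | 8, 11, 9, 13 |
| Friday | 0, 10, 19, 28, 41 | 10, 9, 9, 13 |

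No gap is 7 days. Grading every five sessions would fall after sessions 5, 10, 15, 20, 25 and 30. A course at the stated minimum has 50/2 = 25 sessions, so its last grading is after session 21.

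**3. Chance that an episode falls wholly between visits.** For an episode of D days starting at random within a gap of G days, the missed share is max(0, 1 − D/G). D and the length of suspension are assumptions.

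| Gap | 7-day episode | 10-day | 14-day |
|---|---|---|---|
| 9 days | 22% | 0% | 0% |
| 11 days | 36% | 9% | 0% |
| 13 days | 46% | 23% | 0% |
| 11 days plus a 7-day suspension = 18 | 61% | 44% | 22% |
| 11 days plus a 14-day suspension = 25 | 72% | 60% | 44% |

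Without suspension, episodes of 14 days or more are always seen. With suspension they need not be.

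**4. Effect on the comparison, under assumed miss rates.**
- 20% missed in both arms: 0.8 × 60% = 48% and 0.8 × 21% = 16.8%. The risk difference falls from 39 to 31.2 points. For the same cost difference, the ICER per case avoided is multiplied by 39/31.2 = 1.25. Approximate power at 25 per group falls from 82% to 66%.
- 20% missed in controls only: 48% versus 21%, a difference of 27 points, and power of about 52%.
- An 11-day gap with 10-day control episodes and 7-day laser-arm episodes: 60% × 10/11 = 54.5% and 21% × 7/11 = 13.4%. The difference is 41.2 points, larger than the planned 39.

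The three cases do not agree on direction.

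**The case against.** **Direction.** A reader might infer that the loss falls mainly on controls and understates the laser effect, because controls have the higher assumed rate and are the only arm with a stated suspension provision. The documents do not establish this. If laser speeds healing, severe episodes in the laser arm may be shorter and more often missed per case; the last example above then overstates the effect. Suspended laser-arm participants are equally ungraded.

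**Size.** No episode length is given. Severity that depends on the number of sessions fits persistence under continuing RT at least as well as brief episodes, and 14-day episodes are caught if RT is not interrupted. The planning rates come from a cited source and may already reflect some visit schedule, so subtracting missed cases could count the loss twice. The article plans a Mann–Whitney test on severity, not the two-proportion test behind the power figures. A large power loss is therefore not shown.

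**Records.** The costs section already retrieves severe episodes from hospital records, and the cost-effectiveness section does not restrict incidence to scheduled photographs. This stands in part: a data source exists, but it is named for costs, and it uses the WHO scale alone rather than NCI and/or WHO.

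**Rank of the ICER.** Calling the severe-OM ratio the main one goes beyond the text, which ranks none. The quality-of-life ratios use only baseline and session 30, so extra questionnaires in between would not enter them.

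**Condensation.** An article may leave unscheduled assessments to the full protocol. But the time points are fully stated here and repeated for OM, quality of life and saliva, and the implied weekly interval conflicts with the stated fractionation.

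**Conclusion.** The point holds in a limited form. Gaps between gradings are 8 to 13 days, not weekly, and no grading is stated when RT is suspended for severe OM. As written, the plan can classify as never severe a participant whose severe OM stopped RT, while counting that episode's costs. This follows from the text and needs no assumption about duration.

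How often it happens, and which arm loses more, cannot be derived from the documents. The 25% rise in the ICER rests on an assumed 20% loss in both arms and an unchanged cost difference. The missed shares rest on assumed episode lengths and random onset. They show that the loss could matter, not that it does. The change is worthwhile because it is cheap; it is not a condition for the trial to proceed.

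**What to change.** Apply identically in both arms, with no change to treatment.

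1. On the day RT is suspended for OM, and before any laser in that interval, take the standard photograph set for grading by the blinded assessor. Count a participant as severe if severe at any assessment.
2. Add a photograph set at session 25, or correct the word *weekly*. Session 25 falls on elapsed day 32 (Monday start) or 34 (other starts), which splits the last gap into 4 and 7 or 6 and 7 days. It also serves 25-session courses. The earlier gaps stay at 8 to 11 days, so the wording should be corrected in any case.
3. For participants already treated (recruitment began in August 2017), run a sensitivity analysis that counts as events the charted suspensions for severe OM and the severe episodes already retrieved for costing. ICER costs and effects then refer to the same cases.

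The cost is a short amendment, which may need to go to both ethics committees, and a few more images to grade, with no new staff. The downside is a mix of assessment schedules: later participants have more looks, and so does the arm with more suspensions. The photographs are taken by the researcher who delivers the laser, so grading must stay with the blinded assessor. Report the number of graded sets per participant by arm, and the result on the scheduled visits alone beside the result on all assessments.

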### Randomization and blinding/masking

Participants will be randomly assigned into two groups: group 1 (PBMT, five times per week) and group 2 (control). A computer-based random number generator (www.randomizer.org) will be used to assign the participants to the study groups. Simple randomization will be performed with an allocation ratio of 1:1. The sequence will be generated by an independent collaborator. The letters A and B will be used to determine the group: A = intervention and B = control. The sequence will be concealed in consecutively numbered opaque envelopes. Each envelope will be opened at the time of the first RT session. The participants will be blinded to the allocation group. In the control group, a sham laser will be used; the participants will hear the characteristic sound of the equipment but no irradiation will be performed. The researcher responsible for assessing the OM will also be blind regarding the study group and will not have contact with the participants since the assessment will be carried out using the photographs of the participants.

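### The WHO component of severe oral mucositis cannot be graded from photographs alone, so the combined NCI and/or WHO endpoint is only partly scorable as described

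*Protocol article*

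**What the plan says.** All places are in the protocol article.

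- **Who grades, and from what.** Under Randomization and blinding/masking, the assessor is blinded and "will not have contact with the participants since the assessment will be carried out using the photographs of the participants". Oral mucositis evaluation adds that the researcher who delivers the laser takes the intraoral pictures and stores them for grading later.
- **The scales.** Oral mucositis evaluation uses both WHO and NCI. WHO grade 2 is erythema and ulcer with solid and liquid diets both tolerated. The next two grades are "3, ulcers and liquid diet only; 4, oral alimentation is impossible". The NCI grades, as defined there, rest on visible signs: erythema, ulcer size and contiguity, necrosis and bleeding.
- **The endpoint.** "In this study, OM will be considered severe when classified with grades 3 or 4 according to the NCI and/or WHO scales".
- **Its uses.** Severe OM is the basis of the sample size (Participants), an effectiveness measure (Outcomes) and the denominator of the first incremental cost-effectiveness ratio, or ICER (Cost-effectiveness analysis).
- **A second definition.** Costs due to severe OM counts WHO grades III and IV only, with data taken from hospital records.

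**The concern.** WHO grade 2 is separated from grade 3 by what the participant can eat, and grade 4 is defined by oral intake alone. The assessor has neither the participant nor any stated record of diet. The WHO grade must therefore be guessed, left out, or completed from someone else's information.

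The nearest other source is the laser operator. The article does not list this person as blinded, and the operator has to know whether to irradiate or simulate. Diet status from that source would put the claimed blinding of the WHO component at risk.

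At stake are the count of severe cases in each arm, the power that rests on it, and the number of severe cases avoided, by which the first ICER is divided.

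**Working it through.** **1. What a photograph can settle**

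| Photograph shows | Scales joined by 'or' | Scales joined by 'and' |
|---|---|---|
| NCI 3 or 4 | Severe | Undetermined: WHO 3-4 not confirmed |
| NCI below 3 | Undetermined: WHO could be 3 or 4 | Not severe |

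Each reading leaves one of the two rows open. Under 'or' it is the non-severe call, on which a count of prevented cases depends. Under 'and' it is every severe case. The practical weight under 'or' falls on NCI grade 2, where ulcers are visible and WHO 2 and WHO 3 differ by diet.

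**2. The plan's own sample size**

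Inputs, all from Participants:
- "The 95% significance level (1 – α error type I"): alpha 0.05. Sidedness is not stated; two-sided is assumed.
- "a study power of 80"%.
- "prevalence of severe OM of 60% for the control group and 21% for the PBMT group (OR = 0.18").
- "a 1.0 ratio of unexposed/exposed".
- "an additional 10% was considered to compensate for possible loss to follow-up": not part of the 25 per group.

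Odds ratio check: (0.21/0.79)/(0.60/0.40) = 0.177, which agrees with 0.18.

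Mean rate p̄ = (0.60 + 0.21)/2 = 0.405; difference d = 0.39.

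Kelsey formula: n = (1.960 + 0.842)² × 2p̄(1 − p̄)/d² = 7.849 × 0.48195/0.1521 = 24.87, so 25 per group and 50 in total, as stated. The formula with separate variances under null and alternative gives 24 per group, 48 in total.

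**3. Power at 25 per arm**

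Power = Φ{[d√n − 1.960√(2p̄(1 − p̄))]/√(p1(1 − p1) + p2(1 − p2))}

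At 60% vs 21%: (1.950 − 1.361)/0.637 = 0.925, power 82.3%.

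**4. Illustration: WHO left out, NCI from photographs kept**

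Assume that photographs capture a share c of the severe cases, equal in both arms, and create no false positives. The observed rates are then 0.60c and 0.21c. The values of c are assumptions; the documents give none.

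| c | Control vs laser | Calculation | Power at 25 per arm | Total N for 80% power |
|---|---|---|---|---|
| 1.0 | 60.0% vs 21.0% | (1.950 − 1.361)/0.637 = 0.925 | 82.3% | 48 |
| 0.9 | 54.0% vs 18.9% | (1.755 − 1.334)/0.634 = 0.664 | 74.7% | 58 |
| 0.8 | 48.0% vs 16.8% | (1.560 − 1.297)/0.624 = 0.421 | 66.3% | 70 |

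The ICER denominator shrinks with c, from 0.390 to 0.351 or 0.312. For a fixed cost difference the ratio rises by 1/0.9 = 1.11 or 1/0.8 = 1.25.

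**The case against.** The strongest reply is that the NCI scale carries the endpoint. Its grades 3 and 4 are visual, so under 'or' any such participant can be scored severe from pictures. This stands. A reader might infer that the endpoint cannot be scored at all; the documents do not support that. What the reply does not rescue is the non-severe call under 'or', or the severe call under 'and'.

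A second reply is that an article condenses the full protocol, and a diet record may exist there. That is possible. But the article is not merely silent: it gives photographs without contact as the method, and a scale which that method cannot grade.

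Other stronger readings also fail:

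- **A larger loss of power.** One could apply an assumed sensitivity and specificity to the whole endpoint and obtain much lower power. That treats cases already settled by NCI as guessed and requires false positives, with no figure in the documents to support either. If the operator supplied the grades, error could differ by arm and no equal-error model would apply. Even the milder figures above are a proxy, because Statistical analysis of data plans a Mann-Whitney test for OM severity.
- **An effect on the severe-OM costs.** These come from hospital records, so the photograph problem is not shown to reach them. The conflict there is one of definition: WHO III-IV in the cost section against NCI and/or WHO in the endpoint.
- **Photographic detail.** No size reference is mentioned for the 1.5 cm NCI boundary, but an article may leave such detail out. The dorsal tongue is irradiated and not listed among the photographed sites; this is true but secondary, since no rule requires every irradiated site to be photographed.

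**Conclusion.** The point holds for the WHO component. The stated method cannot deliver WHO grades 2, 3 and 4, and the combined endpoint is only partly scorable under either reading of 'and/or'. Taking diet status from the laser operator would close the gap at the risk of the blinding claimed for it.

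The stated sample size of 50 reproduces and is not in question. The size of the damage cannot be fixed from the documents, because they do not say how many severe cases would be severe on WHO alone. Power of about 75% or 66%, against 82%, is an illustration. It rests on capture of 90% or 80%, equal in both arms, no false positives, a two-sided 0.05 level and 25 evaluable participants per arm.

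**What to change.** 1. **Define the blinded severe-OM endpoint as NCI grade 3-4 from photographs for all participants, and make WHO secondary.** Recruitment began in August 2017 (Trial status), and this definition also covers those already assessed, so early and late participants are graded alike.
2. **Add one participant-completed diet item for WHO** (solid / liquid only / no oral intake) at the five visits where the questionnaires are already given, and pass it to the assessor with the coded photographs. Participants are blinded by the sham procedure, so the answer is blinded too. Where a participant needs help to answer, the helper should not know the allocation.
3. **Replace 'and/or' with one rule**, and reconcile it with the WHO III-IV definition in Costs due to severe OM, so that the clinical and cost analyses count the same event or state why they do not.

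**Cost:** one extra question and a protocol amendment. WHO grades will be missing or unblinded for participants assessed before the change. An NCI-only endpoint also accepts the loss illustrated above to the extent that some cases are severe on WHO alone. The Participants section does not say which scale the 60% and 21% refer to, so the amendment should state whether they apply to the NCI definition.
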